**Table 1. Evaluation Schedule of Assessments and Measures by Time Point**

|                                                                                    | 1wk (R) | 3wk (I) | 8wk (I/R) | 16wk (R) |
|------------------------------------------------------------------------------------|---------|---------|-----------|----------|
| Anthropometry                                                               |         |         |           |          |
| Anthropometry - Baby                                                               | X       | X       | X         | X        |
| Anthropometry - Mother                                                             |         | X       | X         | X        |
| Anthropometry - Father                                                             |         | X       | X         | X        |
| Sleep Outcomes                                                              |         |         |           |          |
| Parent report of infant sleep - Brief Infant Sleep Questionnaire (BISQ)            |         | X       | X         | X        |
| Parent report of own sleep – Insomnia Symptom Questionnaire (ISQ)                  | X       |         | X         | X        |
| Maternal Actigraphy                                                                |         |         | X         |          |
| Infant Actigraphy                                                                  |         |         | X         |          |
| Infant Soothe and Feeding                                                   |         |         |           |          |
| Infant soothing – Babies Need Soothing                                             |         |         | X         | X        |
| Infant temperament - Infant Behavior Questionnaire                                 |         |         |           | X        |
| Feeding frequency - Babies Need Feeding                                            |         | X       | X         | X        |
| Baby's eating behavior – Baby Eating Behavior Questionnaire (BEBQ)                 |         |         |           | X        |
| Parent Outcomes                                                             |         |         |           |          |
| Parenting self-efficacy - Karitane Parenting Confidence Scale                      |         |         | X         | X        |

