| Maternal feeding practices and beliefs – Infant Feeding Style Questionnaire (IFSQ) |         |         | X         | X        |
| Maternal depression – CES-D                                                        | X       |         | X         | X        |
| Self-reported physical health                                                      |         |         |           | X        |

|                                                                         |   |   |   |   |
|-------------------------------------------------------------------------|---|---|---|---|
| Child Safety Outcomes                                                   |   |   |   |   |
| Safe sleep practices – Fowler                                           | X |   |   | X |
| Child safety practices – Framingham Safety Survey                       |   |   |   | X |
| Stress-Support Moderators                                               |   |   |   |   |
| Maternal Personality – Mini IPIP                                        | X |   |   |   |
| Family Background – Risky Families Questionnaire                        | X |   |   |   |
| Financial strain/employment – Assorted questions                        | X |   |   |   |
| Discrimination – Schedule of Racist Events                              | X |   |   |   |
| Romantic relationship characteristics – Assorted questions              | X |   | X | X |
| Co-parent relationship characteristics – Coparenting relationship scale |   |   |   | X |
| Social support – Social Provisions Scale                                | X |   |   |   |
| Family routines - Confusion, Hubbub and Order Scale (CHAOS)             |   |   | X |   |
| Demographics and Health History                                         |   |   |   |   |
| Family demographics, maternal/infant health                             | X |   |   |   |
| Intervention-Related Variables                                          |   |   |   |   |
| Co-parent involvement in intervention                                   |   | X | X |   |
| Implementation quality                                                  |   | X | X |   |

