Mothers who are involved in a romantic relationship will be asked to rate the following: (1) Relationship Satisfaction, using the 4-item Couples Satisfaction Index, (2) Conflict with Romantic Partner, using the 5-item Hostility Scale, (3) Warm, Caring, and Affectionate Behaviors, (4) Dedication Commitment, a 4-item scale assessing the desire to persist in the relationship despite obstacles, (5) Dissolution Risk, two items assessing thoughts of ending the relationship, and (6) Relationship Length and History, including how many times the current relationship has ended/resumed.

*Coparent relationship characteristics.* All mothers will also report on who is involved in coparenting (e.g., child's father, child's grandmother). Our feeding surveys will assess the proportion of feedings given by the mother as well as other caregivers. We will also assess aspects of the coparenting relationship (e.g., "My partner and I have different ideas regarding our child's eating, sleeping, and other routines") using selected questions from the Coparenting Relationship Scale.

*Social support.* Mothers will also be asked to rate the social support they receive from people other than their partner and/or coparent using the Social Provisions Scale.

*Family routines.* We will assess the extent to which parents report that there is order and routine versus chaos and confusion in their home using selected questions from the Confusion, Hubbub, and Order Scale.

*COVID-19 Impact Survey.* This measure will be added to the study procedures for the 16 week (final) visit for 24 participants active during the hold on face-to-face research and will assess COVID-related psychosocial stressors and impacts. Following the resumption of new recruiting in summer 2020, this measure will be administered at the 1 week visit for all new participants.

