#### *b. Describe and explain the study design:*

The study design is a randomized controlled trial. This trial will deliver a responsive parenting intervention (Sleep SAAF) that builds upon our previously tested Soothe/Sleep curriculum to provide information on safe sleep practices, how to soothe, how to distinguish hunger from

other distress, how to promote self-soothing, and bedtime routines. The responsive parenting intervention will be compared to a safety control group. To promote uptake of program content, the programs will be delivered across 2 sessions at **3-weeks and 8-weeks postpartum**, allowing for increased dosage of this critical component. Assessments will be conducted at 1-week postpartum, 3 weeks postpartum, 8 weeks postpartum, and 16-weeks postpartum (final growth outcomes).

The intervention group will be compared to a child safety control group receiving an equal number of visits, which will be focused on child and sleep safety and should not affect infant weight gain. Both interventions will be delivered in the home setting by African American community research associates (CRAs) who are employed and trained by UGA's Center for Family Research (CFR). CRAs will also conduct data collection visits at participants' homes; when possible, the research visits (1 and 16 weeks) and the intervention visits (3 and 8 weeks) will be conducted by different CRAs. Self-report data will be gathered using a secure, web-based survey interface, Qualtrics. When preferred, audio computer-assisted self-interviewing (ACASI) software will be used to support data collection. ACASI elicits less social desirability bias and more accurate reports on sensitive issues than face-to-face interviews or written surveys. Video and audio enhancements guide respondents through the survey; literacy is not an issue. CRAs will receive extensive training on the implementation of curriculum activities. They will meet regularly with the Project Coordinator and Intervention Coordinator and participate in yearly refresher trainings. Our experienced data collection staff have successfully implemented these protocols in multiple projects.

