| 
age z-score > +0.67, as described by Ong and Loos. This increase corresponds to crossing adjacent major centile lines on the standard CDC growth charts. The analysis for these rapid weight gain scores will be a repeated measures analysis, assessing the intervention effects on rapid weight gain scores from age 3 weeks up to age 16 weeks. The analysis will use generalized estimating equations (GEE) with a logit link, an extension of logistic regression which allows for repeated measurements on binary data, and will include infant weight adjusted for gestational age as a covariate. Because it is unlikely that within an 16-week period we will have many infants who meet the criteria for rapid weight gain based on the upward percentile crossing approach, we will also calculate conditional weight gain scores (CWG) following the method of Griffiths and colleagues, as described in our recent work.
 
Specific Aim 2: The Effects of Sleep SAAF on Parental and Infant Behaviors that Mediate Effects on Infant Growth. In Specific Aim 2 the primary outcomes are parental behaviors (parental self-efficacy, sleep/soothing practices, feeding practices, family chaos) and infant behaviors (sleep, soothing, and feeding) targeted by the intervention that may mediate effects on infant growth. We examine these effects in several steps.
 
First, we will examine differences between the Sleep SAAF and control groups in these outcomes at two time points post-intervention (8- and 16- weeks postpartum) using the linear mixed-effects model described above. The linear mixed-effects model will include intervention group and infant weight adjusted for gestational age. These analyses will test whether the Sleep SAAF group and the control group differ in these behaviors post-intervention and will be used to identify variables for the formal test of mediation.
 
Second, we will examine whether parent and infant behaviors mediate infant weight outcomes. We will test these hypotheses using structural equation modeling (SEM). The first step in demonstrating mediation is to establish the effects on mediating and distal outcomes, as we described above. We then specify mediators as indirect effects in a path model. Intervention condition will be dummy coded and specified as a predictor of infant and parental behaviors, which in turn predict infant weight and weight gain. The significance of the mediating process will be tested using the Sobel or bootstrapping methods.
 
Specific Aim 3: Moderation of Intervention Effects by Individual and Contextual Factors. In Specific Aim 3 we consider whether individual (depressive symptoms) and contextual (socioeconomic stressors, race-based stressors, romantic relationship characteristics, coparent relationship characteristics, social support) factors at 1 week postpartum moderate program effects. These factors will be included in the analyses described above to determine whether they moderate intervention effects on weight outcomes (Specific Aim 1) and parental and infant behaviors (Specific Aim 2).
 
As an exploratory analysis, we will also evaluate whether the individual and relationship variables differ between the Sleep SAAF group and the control group at 16 weeks postpartum. Doing so will allow us to examine whether improving infant sleep and soothing has secondary benefits for mothers' individual and relationship functioning.
 |                                         |

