
|                                                                                                                                                                                                                                                                                                                                                                                                                                                                                                                                                                                                                                                                                                                                                       |                                 |
|-------------------------------------------------------------------------------------------------------------------------------------------------------------------------------------------------------------------------------------------------------------------------------------------------------------------------------------------------------------------------------------------------------------------------------------------------------------------------------------------------------------------------------------------------------------------------------------------------------------------------------------------------------------------------------------------------------------------------------------------------------|---------------------------------|
| 
The primary outcomes for this study will be BMI z scores at 16 weeks (Specific Aim 1) and parent and infant behaviors at 8 weeks and 16 weeks (Specific Aim 2). We used G Power 3.1.9.2 to estimate the smallest intervention effect size we can detect with 80% power, a 5% two-tailed Type 1 error rate, and two groups of 175 each (conservatively assuming 10% attrition over the course of the study). We can achieve 80% power with an effect size <math>d</math> of 0.34. Our recent research showed an effect size of approximately 0.4 for infant nighttime sleep duration at 8 weeks and for infant conditional weight gain at 6 months, suggesting that we will have sufficient power in our sample to detect intervention effects.
 |                                 |

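### Family chaos is a primary Aim 2 outcome to be compared at 8 and 16 weeks, but the schedule collects it at 8 weeks only, so the 16-week comparison cannot be made

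*Supplement*

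**What the plan says.** All references are to the later of the two protocol versions in the Supplement.

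- **Section 7.a, Specific Aim 2, outcome list.** "In Specific Aim 2 the primary outcomes are parental behaviors (parental self-efficacy, sleep/soothing practices, feeding practices, family chaos", followed by infant sleep, soothing and feeding. All are described as behaviours the programme targets and as possible mediators of its effect on growth.
- **Section 7.a, Specific Aim 2, first analysis step.** A linear mixed-effects model compares the arms "in these outcomes at two time points post-intervention (8- and 16- weeks postpartum". No exception is made for family chaos. The results also decide which variables enter the formal mediation test.
- **Section 7.b, Power.** The Aim 2 primary outcomes are "parent and infant behaviors at 8 weeks and 16 weeks (Specific Aim 2", again without exception, though this sentence names no individual behaviour.
- **Section 6.a, Table 1.** The columns are "1wk (R) | 3wk (I) | 8wk (I/R) | 16wk (R"). The row "Family routines - Confusion, Hubbub and Order Scale (CHAOS") has one mark, in the 8-week column.
- **Section 6.a, measure descriptions, under Stress-Support Moderators.** Family routines are measured as "order and routine versus chaos and confusion in their home using selected questions from the Confusion, Hubbub, and Order Scale". No time point is given there.
- **Section 6.b.** "the programs will be delivered across 2 sessions at 3-weeks and 8-weeks postpartum".

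**The concern.** The analysis text promises two post-intervention comparisons of family chaos, and the data collection plan supports one. If both stand, the analyst reaches the 16-week comparison with nothing to analyse and has to decide then how to handle a named primary outcome: drop the visit, report the 8-week result alone, or drop the variable. That decision should be made in the plan, before the data are seen.

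Two consequences follow. The only chaos reading is taken at the visit where the second session is delivered, so whether household routine changes or holds in the weeks after that session is never observed. And because the Aim 2 group comparisons select the mediators, chaos would be screened on one visit while the other behaviours are screened on two.

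**Working it through.** The point rests on no sample size or power figure, so there is no stated number to reproduce. The check sets the Aim 2 text beside Table 1.

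**Step 1. Is the table read correctly?** Its layout was broken in conversion, so the column alignment was tested on other rows in the same part of the table. Implementation quality is marked in columns 2 and 3, which matches delivery at 3 and 8 weeks in section 6.b. Safe sleep practices are marked in columns 1 and 4, the two research visits at 1 and 16 weeks. Column 3 is therefore 8 weeks, and the single CHAOS mark is in column 3.

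**Step 2. Which Aim 2 measures have both visits?**

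| Measure in Table 1 | 1 wk | 3 wk | 8 wk | 16 wk |
|---|---|---|---|---|
| Parenting self-efficacy (Karitane) | – | – | X | X |
| Babies Need Soothing | – | – | X | X |
| Infant Feeding Style Questionnaire | – | – | X | X |
| Infant sleep (BISQ) | – | X | X | X |
| Babies Need Feeding | – | X | X | X |
| Family routines (CHAOS) | – | – | X | – |

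Among these measures, only CHAOS lacks the 16-week assessment. Required by section 7.a: 2 (8 and 16 weeks). Scheduled: 0 + 0 + 1 + 0 = 1. Shortfall: 2 − 1 = 1, the 16-week assessment, for every dyad.

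**Step 3. Is it collected elsewhere?** The 16-week home visit in section 6.a lists questionnaire measures generically and refers to Table 1 for what is assessed when. No other text in this version schedules CHAOS at 16 weeks.

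**Step 4. Can the missing-data method recover it?** Section 7.a uses full-information maximum likelihood. Let y8 and y16 be a dyad's two scores. With y16 unobserved, the dyad contributes ∫ f(y8, y16 | arm) dy16 = f(y8 | arm), which does not contain the 16-week means or the 8-to-16-week covariance. When y16 is missing for some dyads, those with both scores supply these parameters. Here no dyad has both, so the likelihood carries no information on a 16-week arm difference.

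**Step 5. What is lost in time?** The second session and the only reading fall at the 8-week visit, and follow-up ends at 16 weeks. The unobserved interval is 16 − 8 = 8 weeks.

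**Step 6. What survives?** The arm comparison at 8 weeks uses scheduled data. For mediation, an 8-week value precedes 16-week weight, so that path can still be fitted.

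**The case against.** The best case on the other side is that this is a small inconsistency between text and schedule. Chaos is not named in the Aim 2 hypothesis or among the parenting behaviours in the conceptual-model text, the BMI z-score outcome does not depend on it, and the 8-week analyses survive. That is fair and limits the weight of the point. It does not remove the contradiction between section 7.a and Table 1. Appendix 4, which holds the measures, is not shown, so the documents establish that no 16-week assessment is scheduled in Table 1, not that none was ever taken.

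Four stronger readings are tempting, and the documents do not support them.

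- **That chaos will be used as a moderator, conditioning on a consequence of treatment.** Table 1 places the row under Stress-Support Moderators, but Aim 3 gives its own list, which omits chaos and ends "coparent relationship characteristics, social support) factors at 1 week postpartum moderate program effects". CHAOS is not measured at 1 week. The table's headings do not fix analysis roles: maternal depression sits under Parent Outcomes, yet depressive symptoms are an Aim 3 moderator.
- **That the 8-week reading reflects only one session.** The 8-week visit lists programme delivery first and questionnaires third. What can be said is that the second session has had no time to alter home routine.
- **That a fixed fraction of the primary comparisons is lost.** The plan never defines a set of domain-by-visit comparisons, and parental and infant soothing appear to share one scale, so any such fraction would be the reader's own construction.
- **That section 7.b itself names chaos a primary outcome.** It refers only to parent and infant behaviours; the naming is in 7.a.

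**Conclusion.** The point holds as an inconsistency that makes one stated analysis impossible. Family chaos is named as a primary Aim 2 outcome for comparison at 8 and 16 weeks. One of those two assessments is scheduled, and the 16-week comparison cannot be made for any dyad. The planned missing-data method does not help.

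The effect is confined to one behavioural outcome. The trial loses the ability to say anything about household routine after the 8-week visit. It keeps the 8-week comparison, the 8-week mediator and all weight outcomes. The conclusion assumes that Table 1 is the operative schedule, as section 6.a indicates, and that the 16-week questionnaire contains no CHAOS items beyond it.

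**What to change.** **Preferred.** Add the same selected CHAOS items to the existing 16-week questionnaire and mark the 16-week column in Table 1. The visit is already held, so the cost is a few more self-report items per mother.

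**For dyads already past 16 weeks, or if the items are not added.** Amend section 7.a so that family chaos is an 8-week-only outcome and candidate mediator, analysed as a single-visit comparison. Exclude it explicitly from the set compared at 8 and 16 weeks in 7.a and 7.b. This costs a sentence or two and no data collection, but the plan then gives up any claim about routine after the second session.

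**Optional.** Move the Table 1 row from Stress-Support Moderators to an outcomes heading. This is tidying only, because Aim 3 does not list chaos as a moderator.

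### Aim 3 names coparenting as a 1-week moderator and Aim 2 compares family chaos at 16 weeks, but Table 1 schedules neither measurement

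*Supplement*

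**What the plan says.** All references are to the later protocol version in the supplement, the one that recruits 375 dyads.

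**Moderators.** Section 7a, Specific Aim 3, lists one individual factor (depressive symptoms) and five contextual ones (socioeconomic stressors, race-based stressors, romantic relationship, coparent relationship, social support). It fixes when they are taken: "coparent relationship characteristics, social support) factors at 1 week postpartum moderate program effects". They are to be tested as moderators of the effects on weight (Aim 1) and on behaviours (Aim 2).

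**Schedule.** The visit columns of Table 1 (Section 6a) read "1wk (R) | 3wk (I) | 8wk (I/R) | 16wk (R". The coparenting row is "Co-parent relationship characteristics – Coparenting relationship scale | | | | X": one mark, in the last column.

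**Exploratory outcomes.** Section 7a also plans to test whether "individual and relationship variables differ between the Sleep SAAF group and the control group at 16 weeks postpartum".

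**Family chaos.** Specific Aim 2 counts family chaos among its primary outcomes and will examine "differences between the Sleep SAAF and control groups in these outcomes at two time points post-intervention (8- and 16- weeks postpartum". The power statement in Section 7b gives the same two visits for the parent and infant behaviours. In Table 1 the row "Family routines - Confusion, Hubbub and Order Scale (CHAOS" is marked at 8 weeks only.

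**The concern.** A moderator has to be measured before the programme can act on it. Aim 3 respects this by fixing its moderators at 1 week, but the schedule provides no coparenting score at that visit. An analyst who reaches this test must either omit it or use the only score available, from 16 weeks. The second course would give an interaction between treatment and a post-treatment variable, which does not describe which families benefit more. Aim 3 is meant to guide the design of later multi-component programmes, so a result of that kind could mislead.

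The family-chaos gap is simpler. The protocol promises a comparison, for an outcome that it calls primary under Aim 2, at a visit where the scale is not given.

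**Working it through.** No arithmetic beyond counting applies. The check sets the analysis text beside the schedule.

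**1. Do the Table 1 columns line up?** The table is split, and its second block carries no header, but each row there has four cells. Two rows test the alignment. Social support reads "Social support – Social Provisions Scale | X", with its mark in the first cell (1 week). Implementation quality is marked in the second and third cells (3 and 8 weeks), the two visits at which Section 6b says the programme is delivered. The columns match the header.

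**2. Each Aim 3 domain against the 1-week column.**

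| Aim 3 domain | Table 1 measure | 1 week? | Other visits |
|---|---|---|---|
| Depressive symptoms | CES-D | Yes | 8, 16 |
| Socioeconomic stressors | Financial strain/employment | Yes | none |
| Race-based stressors | Schedule of Racist Events | Yes | none |
| Romantic relationship | Assorted questions | Yes | 8, 16 |
| Social support | Social Provisions Scale | Yes | none |
| Coparent relationship | Coparenting Relationship Scale | **No** | 16 only |

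Five of six domains have the baseline measure that Aim 3 needs; one does not.

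**3. Does anything else supply a 1-week coparenting score?** The measure description in Section 6a gives no time point. The Home Visit 1 list mentions questionnaires without naming them. Coparent involvement in the intervention (3 and 8 weeks) is a different variable and is itself post-randomization. The 1-week romantic-relationship items form a separate domain in the Aim 3 list. Full-information maximum likelihood, the stated method for missing data, cannot supply a variable with no scheduled observations.

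**4. Where does the 16-week score fall?** Randomization is at Home Visit 1 (7–10 days) and the sessions are at 3 and 8 weeks. The only coparenting score comes after all three, at the same visit as the primary BMI z score. The documents give two reasons to think that it could respond to the programme. Coparents are encouraged to attend and receive the intervention, and the sample item in the measure description concerns disagreement over the child's eating, sleeping and routines.

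**5. Aim 2 constructs against the 8- and 16-week columns.** Aim 2 names four parental constructs (self-efficacy, sleep/soothing practices, feeding practices, family chaos) and three infant ones (sleep, soothing, feeding). The Karitane scale, BISQ, Babies Need Soothing, IFSQ and Babies Need Feeding are all marked at both visits. CHAOS is marked at 8 weeks only. On that listing there are 7 × 2 = 14 construct-by-visit comparisons, and 1 of the 14 has no data.

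**The case against.** A reader might infer that Aim 3 will test moderation by the 16-week coparenting score, or that one score will serve as both outcome and moderator. The documents do not support either reading. Aim 3 restricts its moderators to 1 week, and no passage proposes the later score for that role. The exploratory analysis speaks of relationship variables without naming coparenting, and the romantic-relationship measures at 16 weeks would satisfy the phrase. Post-treatment moderation is therefore a risk of substitution, not a stated analysis.

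It can also be said that the coparenting domain is wider than the scale. Mothers report who is involved in coparenting, with no visit stated, and the measures appendix is not among the documents shown. Some descriptive 1-week information may exist. That limits the claim to the scale in Table 1, but it does not supply a coparenting relationship score.

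On family chaos, the 8-week comparison can go ahead, and an 8-week score still precedes the 16-week weight outcome for the mediation model. The count of 14 depends on how overlapping soothing constructs are grouped. Both remarks are fair, but the 16-week comparison still has no data.

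Finally, the defect touches neither the primary BMI z analysis, the power statement for that outcome, nor the intention-to-treat approach. That is right, and it sets the severity.

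**Conclusion.** The point stands as a contradiction within the current version between the analysis text and the assessment schedule. One of six Aim 3 moderator analyses cannot be run as written, and one Aim 2 comparison (16-week family chaos) has no data. Five of the six moderator domains and the 8-week family-chaos comparison are unaffected, as is the primary Aim 1 analysis. Severity is moderate.

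The conclusion assumes that Table 1 is the full schedule for these two scales; nothing else in the documents shown places either of them at another visit. The warning about interpretation is conditional: it applies only if the 16-week coparenting score is put in place of the missing baseline.

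**What to change.** **Coparenting**

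- For dyads not yet enrolled, add the selected Coparenting Relationship Scale items to the 1-week visit and to Table 1. The Home Visit 1 list puts randomization and arm-specific materials before the questionnaires, so state that these items are completed before allocation is revealed. Otherwise the score would not be a clean baseline.
- Exclude dyads without a 1-week score from the coparenting moderation test. If enrolment is largely complete, drop coparenting from the Aim 3 list instead. The documents do not say how many dyads remain to be enrolled, though they already refer to recruiting resumed in summer 2020, so this may be the realistic course.
- In either case, state that the 16-week score is used only as an exploratory outcome and never as a moderator.

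**Family chaos**

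- Either add CHAOS at 16 weeks, or amend Aim 2 and the power statement so that family chaos is compared at 8 weeks only. The second option costs nothing to collect, but the 8-week score is taken at the same visit as the second session, so that comparison would mainly reflect the first.

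**Cost.** A few questionnaire items at existing visits, edits to Table 1 and Section 7, and the loss of already enrolled dyads for that one moderator.
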